## Abstract

**Background:**

Patients with lower extremity amputation frequently suffer from socket-related problems. This seriously limits prosthesis use, level of activity and health-related quality of life (HRQoL). An additional problem in patients with lower extremity amputation are asymmetries in gait kinematics possibly accounting for back pain. Bone-anchored prostheses (BAPs) are a possible solution for socket-related problems. Knowledge concerning the level of function, activity and HRQoL after surgery is limited.

The aims of this ongoing study are to: a) describe changes in the level of function, activity, HRQoL and satisfaction over time compared to baseline before surgery; b) examine potential predictors for changes in kinematics, prosthetic use, walking ability, HRQoL, prosthesis comfort over time and level of stump pain at follow-up; c) examine potential mechanisms for change of back pain over time by identifying determinants, moderators and mediators.

**Methods/design:**

A prospective 5-year longitudinal study with multiple follow-ups. All adults, between May 2014 and May 2018, with lower extremity amputation receiving a press-fit BAP are enrolled consecutively. Patients with socket-related problems and trauma, tumour resection or stable vascular disease as cause of primary amputation will be included. Exclusion criteria are severe cognitive or psychiatric disorders. Follow-ups are planned at six-months, one-, two- and five-years after BAP surgery. The main study outcomes follow, in part, the ICF classification: a) level of function defined as kinematics in coronal plane, hip abductor strength, prosthetic use, back pain and stump pain; b) level of activity defined as mobility level and walking ability; c) HRQoL; d) satisfaction defined as prosthesis comfort and global perceived effect. Changes over time for the continuous outcomes and the dichotomized outcome (back pain) will be analysed using generalised estimating equations (GEE). Multivariate GEE will be used to identify potential predictors for change of coronal plane kinematics, prosthetic use, walking ability, HRQoL, prosthesis comfort and for the level of post-operative stump pain. Finally, potential mechanisms for change in back pain frequency will be explored using coronal plane kinematics as a potential determinant, stump pain as moderator and hip abductor strength as mediator.

**Discussion:**

This study may identify predictors for clinically relevant outcome measures.

**Trial registration:**

NTR5776. Registered 11 March 2016, retrospectively registered.

**Electronic supplementary material:**

The online version of this article (doi:10.1186/s12891-016-1341-z) contains supplementary material, which is available to authorized users.

## Background

The population living with a lower extremity amputation is estimated to grow significantly, in part, due to the aging population and high rates of vascular disease [1]. In the Netherlands, 90–94% of the lower extremity amputations are due to vascular disease, 3% to trauma and 3% to tumour resection [2]. The primary amputation level is transtibial in 49% of the patients, knee disarticulation in 9%, transfemoral in 34% and bilateral in 9% [3]. Approximately 86% of the patients with a lower extremity amputation are fitted with a socket prosthesis (SP) [4]. Within socket prosthesis users, 34–63% have reported suffering from socket-related problems including chronic skin problems and residual limb pain associated with the socket [5–9]. It is well known that the symmetry in spatio-temporal, kinematic and kinetic parameters during gait is reduced in SP users compared to able-bodied persons [10–12]. In addition socket fitting problems [13], decreased hip abductor strength [13–15] and changed muscle activity patterns [16] may be a possible cause for this asymmetry. Gait asymmetry, specifically in the coronal [17–19] and sagittal plane [18], are considered to be associated with secondary complaints such as back pain [20]. Both, socket-related problems and back pain can lead to limited prosthetic use [5, 21] and reduced health-related quality of life (HRQoL) [5, 7].

For patients with a lower extremity amputation who suffer from socket-related problems the prosthesis can be transcutaneously attached to the bone by osseointegration utilizing intramedullary implants, known as bone-anchored prostheses (BAPs) [22]. BAPs are used in patients with a transfemoral [23–30] or transtibial amputation [31–33]. To date, there are two types of implants available: a screw BAP [34, 35] and a press-fit BAP [29, 36]. Both are implanted using two-step surgery techniques, however, for the press-fit BAP the time between surgeries is 4.5 months shorter than for a screw BAP [34, 36]. Additionally, the rehabilitation period is shorter for press-fit BAP because the implant allows more weight bearing in the early post-operative phase [29, 34–36].

An advantage of direct attachment to the bone, regardless of the used BAP method, is that the patient has a better ability to detect vibrotactile and pressure stimuli of the prosthetic limb compared to socket prosthesis users [22, 37, 38]. These stimuli are also known as osseoperception. Although BAP surgery has been performed for over 25 years only eight and generally small longitudinal studies [23, 25, 27–31, 39] assessed the level of function, activity and QoL outcomes of BAP compared to SP use. Various benefits have been found on body functions or structures (hereafter referred to as level of function), level of activity and HRQoL for BAP use compared to SP use [40, 41]. However, functional outcomes seem to be an underexposed part of BAP research to date. This is remarkable, because BAP surgery is an invasive intervention aimed to overcome problems in physical functioning in SP users with socket-related problems. In the SP population, complaints such as back pain may be the result of asymmetries in coronal plane gait kinematics and are possibly related to hip abductor strength deficiencies [20, 42], but have not been researched in the BAP population. Research on the level of satisfaction experienced by the patient with respect to their prosthesis is absent. Similarly, factors associated with outcomes regarding the levels of function, activity, HRQoL and satisfaction of the prosthesis after BAP surgery has not been researched. This study will address the above mentioned outcomes and follow, in part, the ICF classification [41]. The purpose of this manuscript is to detail the study protocol of an ongoing prospective 5-year longitudinal study with multiple follow-ups. The study focuses on patients with a lower extremity amputation who are fitted with a press-fit BAP and complete a standard rehabilitation programme. Through publishing this study protocol we aim to: a) increase the transparency of our data collection; b) prevent publication bias and selective reporting; c) prevent data dredging [43]. The study has four aims:

Aim 1: to describe the change in the level of function, activity, HRQoL and satisfaction in patients with a lower extremity amputation after receiving a press-fit BAP at short-term (six-months and one-year), mid-term (two-years) and long-term (five-years) follow-up in comparison to baseline. We hypothesise that coronal plane kinematics symmetry, hip abductor strength, prosthetic use, mobility level, walking ability, HRQoL and prosthesis comfort will improve over time and that the frequency of back pain will decrease over time.

Aim 2: to examine potential predictors for the change of coronal plane kinematics, prosthetic use, walking ability, HRQoL and prosthesis comfort over time: outcomes that are the main reason why patients choose a BAP The potential predictors which will be included in the analysis are: demographic data, patient characteristics, baseline level of function, baseline level of activity and baseline level of satisfaction (Additional file 1).

Aim 3: to examine predictors for the level of stump pain at short-term, mid-term and long-term follow-up (Additional file 1). In our clinic we see that stump pain after BAP surgery negatively influences outcomes on the level of function, activity, HRQoL and satisfaction. However, we do not have insight in the level of stump pain at follow-up and knowledge concerning predictors for stump pain is absent.

Aim 4: to examine potential mechanisms for changes in back pain at short-term, mid-term and long-term follow-up. We hypothesise that an increase of coronal plane kinematics symmetry will be a possible determinant for a decrease in back pain (Fig. 1). We also hypothesise that stump pain will act as moderator and hip abductor strength will act as mediator.

**Fig. 1 Fig1:**
[figure not shown]
Causal model for change of back pain

The short-, mid- and long-term outcomes and the results of the various aims of this study will be presented in separate articles.

## Methods and design

This is an ongoing prospective 5-year longitudinal study with multiple follow-ups. All assessments are part of usual care for patients with a lower extremity amputation following BAP surgery.

### Study population

All patients who are eligible for a press-fit BAP in the Netherlands undergo surgery in one hospital (Radboud university medical centre). All consecutive patients in our centre, between May 2014 and May 2018, undergoing BAP surgery are eligible for this study. Patients are eligible for press-fit BAP surgery if: a) they are adults with a lower extremity amputation suffering from socket-related problems contributing to limited prosthetic use; b) the cause of primary amputation is congenital or due to a trauma, tumour resection or stable vascular disease. Exclusion criteria for surgery are the presence of severe cognitive or psychiatric disorders. A multidisciplinary team including a surgeon, rehabilitation physician, physiotherapist and prosthesist assess patients for inclusion for BAP using a standard procedure as described by Van de Meent et al. [29]. When patients’ medical history reveals a psychiatric history, a psychologist is consulted to assess the patient prior to inclusion.

### Sample size

We will not draw a sample, but aim to include the entire population, which started in May 2014. We expect to have little non-responders as all assessments are part of usual care. This expectation is supported by the fact that we had no non-responders since the start of this study. Based on the average number of surgeries in the Netherlands during the year 2014 and 2015 we expect that 18 patients will be included each year [44]. For our first aim, investigating change over time, we will present the first interim analyses of this growing cohort when we have a minimum of 40 patients at the following time points: one-, two- and five-year follow-up. Press-fit BAP surgery started in the Netherlands in 2009. Between 2009 and 2014, 42 patients received a BAP. Thus at the time of our first interim analyses (mid of 2017) the total Dutch population with a minimum follow-up of one-year will include 82 patients [44]. Although, the sample size of 40 patients appears to be small, the study will have gathered longitudinal data (with a minimum follow-up of one-year) in 49% of the total Dutch population of patients with a press-fit BAP. We expect that this is sufficient to be able to generalise the results to the Dutch population eligible for a press-fit BAP. Of the patients included in this study to date, none have dropped out. We also do not anticipate any high drop-out rates for the remainder of the study as the assessments are part of usual care.

We will use the rule-of-thumb for prediction modelling with multiple factors and assume that we need ten cases per predictor [45]. The various continuous outcomes of interest have a different number of potential predictors (Additional file 1) ranging from three to seven variables. A minimum of 30 subjects are needed for prosthetic use, 40 subjects for HRQoL, 50 subjects for walking ability and prosthesis comfort, 60 subjects for coronal plane kinematics, and 70 subjects for stump pain. Based on these numbers we expect to complete the inclusion of patients for this study around May 2018.

### Intervention

Press-fit BAP surgery involves two surgeries six to eight weeks apart [29, 36]. First, a cementless intramedullary stem is inserted in the femur or tibia and the wound is closed. After osseointegration has been initiated, a second procedure creates a soft tissue stoma with a transcutaneous connector which is bolted into the intramedullary stem. Between the two surgeries the patient is not allowed to use a socket prosthesis but is permitted to ambulate on the sound limb using a walking aid, such as crutches.

All patients start rehabilitation one week after the second surgery. Rehabilitation aims to reach predetermined functional goals. These goals include increasing the level of activity and minimising gait compensation strategies, such as, an unstable pelvis and ipsilateral lateral flexion of the trunk during stance phase. Rehabilitation focuses on improving hip abductor strength, core stability, symmetry in spatio-temporal parameters and symmetry in kinematic parameters. The detailed rehabilitation programme is described elsewhere [46]. The duration of the twice weekly rehabilitation programme (Fig. 2) depends on the level of amputation level and ranges from 4 weeks (transtibial amputation) to 11 weeks (transfemoral amputation). Rehabilitation is prolonged if the patient is improving but has not met the previously determined goals.

**Fig. 2 Fig2:**
[figure not shown]
Flow chart of assessments and interventions

### Ethics

Patients included in this study are informed about the baseline and follow-up assessments by the treating physician during the multidisciplinary out-patient clinic for BAP. A separated document, including a patient information letter and informed consent form is attached to the baseline assessment appointment letter. Informed consent with permission to use the usual care data for research purposes is obtained prior to the baseline assessment. The study is conducted according to the principles of the Declaration of Helsinki (64th version, 19-10-2013). The protocol of this study (registration number 2014/196) was approved by the Ethics Committees of Radboud university medical centre.

### Study procedures and parameters

Patients are assessed by the treating physiotherapist at baseline (preoperatively) and at six-month, one-, two- and five-year follow-up (Fig. 2). The primary outcomes of this study are level of function, activity, HRQoL and satisfaction. Demographics and patient characteristics are obtained from the patients. These variables will be used for descriptive statistics, and some will be used as potential predictors for change of coronal plane kinematics, prosthetic use, walking ability, HRQoL, prosthesis comfort and the level of stump pain at follow-up (Additional file 1).

#### Demographics and patient characteristics

Sex, age, cause of amputation and the time from primary amputation to inclusion are collected at baseline from the patients’ medical file. Level of amputation is obtained at baseline and at six-month follow-up. Body mass index (BMI) accounting for the limb loss using the adjusted body weight [47], residual limb and sound limb characteristics [46, 48] and used prosthesis parts are obtained at baseline and all follow-up time points. Rehabilitation characteristics (the duration in weeks and the number of rehabilitation sessions) are also obtained. Adjusted body weight is calculated with the following formula: actual body weight/(1 minus percentage of the amputated part of the limb). The amputation percentages are: Transfemoral Amputation (TF): 10.1%, Transtibial Amputation (TT)/knee disarticulation (KD): 5.9%, foot amputation: 1.5%, bilateral TF: 20.2%, bilateral TT/KD: 11.8%, bilateral foot amputation: 3.0% and TF combined with TT/KD: 16.0% [47].

#### Level of function

##### Coronal plane kinematics

In unaided walkers, kinematics in the coronal plane are recorded using a video camera (Panasonic HC-X920) during two activities. First, while a patient walks three times up and down a path of 15 m. Secondly, while a patient performs a step exercise with the sound side. The step exercise is performed, two times consecutively using a 11 cm high aerobic power step (Tunturi® New Fitness, Almere, The Netherlands). The kinematics (continuous scale) in coronal plane (in degrees) are assessed using two methods: a) an overall angle between trunk and residual limb during the mid-stance is calculated out of two angle measurements, namely the angle between pelvis and residual limb and the angle between pelvis and trunk. To be able to assess these angles using Dartfish® software (Dartfish, Fribourg, Switzerland), a piece of tape (approximately 1.0 by 1.0 cm) is placed on 1) the anterior superior iliac spine (ASIS) on both sides, 2) the proximal part of the manubrium and 3) 30 cm distal of the ASIS on the ventral side of the residual limb (Fig. 3). The reference points for the position of the tape on the residual limb varies. In patients with a transtibial amputation the middle of the patella is used as a reference for all assessments. At baseline, the middle of the socket is used in patients with transfemoral amputation or knee disarticulation, because the position of the bone in soft tissue is not visible. At follow-up the transcutaneous connector is used in patients with a transfemoral amputation; b) peak pelvis and trunk segment angles during stance phase are measured relative to the laboratory axis using two wireless gyroscopes (Valedo®Motion, Hocoma, Volketswil, Switzerland) on the first vertebrae of the sacrum and 17.5 cm cranial of the distal gyroscope respectively, (Fig. 4) using an applicator. A reproducibility study is now ongoing to assess both angle measurements and will determine which instrument will be used to evaluate the kinematics.

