#### Level of health-related quality of life

The Q-TFA global score (continuous scales: 0–100 points) is used to assess HRQoL and is a summary of three items: perception of function, problems with the current prosthesis and the perception of the current overall amputation situation [29, 50]. A higher score reflects a better HRQoL. All three items are scored on a 5-point likert scale. For patients not using a prosthesis only the single overall question (ordinal scale) is used; ‘*How would you summarize your overall situation as an amputee?*’, with five response alternatives; ‘extremely poor’, ‘poor’, ‘average’, ‘good’ or ‘extremely good’.

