### Statistical analysis

All outcomes will be analysed non-stratified. Additionally, we will stratify for level of amputation and for baseline wheelchair-boundedness when applicable. The size of the subgroups will determine whether statistical tests will be used to analyse the outcomes of the subgroups, or if only descriptives will be presented. All analyses will be performed using SPSS v23 (SPSS Inc., Chicago, Illinois, United States). In all cases, two sided *p*-values <0.05 will be considered to be statistically significant.

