#### Descriptive statistics

Categorical data will be presented as exact numbers. Percentages will be calculated for the various levels. For the continuous data, means and standard deviations will be calculated for normally distributed variables. For data not-normally distributed median and inter-quartile ranges will be used. Missing data will be analysed and imputation techniques will be used where necessary.

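### Kinematics exist only for unaided walkers and the HRQoL global score only for prosthesis users, so the non-stratified change-from-baseline analysis has no fixed population, and the 60 subjects for kinematics need at least 83% of the cohort to walk unaided

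*Protocol article*

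**What the plan says.** **Who is measured.** Coronal plane kinematics: "In unaided walkers, kinematics in the coronal plane are recorded using a video camera". Level of health-related quality of life: "For patients not using a prosthesis only the single overall question (ordinal scale) is used"; prosthesis users get the 0–100 global score, a summary of three items. The TUG and the 6-minute walking test (6MWT) carry no unaided-walker limit.

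**Who is enrolled.** Study population: "All consecutive patients in our centre, between May 2014 and May 2018, undergoing BAP surgery are eligible for this study". Candidates have socket problems that limit their prosthesis use; walking unaided is not required. The question on aids under Mobility level runs from wheelchair to no aid, and Statistical analysis foresees a stratum for patients wheelchair-bound at baseline.

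**How it is analysed.** Statistical analysis: "All outcomes will be analysed non-stratified", with stratified analyses as additions. Aim 1 uses exchangeable GEE and lists kinematics and HRQoL among the continuous outcomes, reported as mean change; each follow-up is compared with baseline. Descriptive statistics: "Missing data will be analysed and imputation techniques will be used where necessary". In the prediction models, the baseline value of each outcome is also a candidate predictor.

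**How many.** Sample size: "we expect that 18 patients will be included each year"; the authors "assume that we need ten cases per predictor"; the largest requirements are "60 subjects for coronal plane kinematics, and 70 subjects for stump pain".

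**The concern.** Whether a patient has a kinematic angle or a global score depends on how well that patient functions, which is what these outcomes are meant to show. A patient on crutches at baseline who later walks unaided contributes to the follow-up mean but not to the baseline mean. A non-user who becomes a user does the same for the global score. The main estimate of change then mixes change within patients with a change in who is measured.

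The tools that the plan names do not settle this. General imputation does not separate a missed assessment from a value that does not exist, and a gait angle imputed for someone who cannot walk unaided has no clear meaning. The wheelchair stratum leaves aided walkers in the other group, and it contains no baseline angle to compare with.

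At stake are the population that the Aim 1 results for kinematics and HRQoL describe, and whether the kinematics prediction model can meet the plan's own ten-per-predictor rule.

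**Working it through.** **1. The plan's own figures.** Ten cases per predictor with 3, 4, 5, 6 and 7 predictors gives 30, 40, 50, 60 and 70, as stated. Accrual is 18 × 4 years (May 2014 to May 2018) = 72, which covers the largest requirement of 70 if every patient can be used.

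**2. Kinematics against accrual.** 60 / 72 = 0.833, so at most 72 − 60 = 12 patients (16.7%) may lack a baseline angle. Because the baseline angle is itself a candidate predictor, a patient without one cannot be used in a model that contains it. The share p of unaided walkers at baseline is not in the document, so it is varied here. The expected number is 72p, the chance of reaching 60 is P(X ≥ 60) with X ~ Binomial(72, p), and the cohort needed is 60 / p, rounded up.

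| Assumed p | Expected number | Predictors at 10 each | P(at least 60) | Cohort needed |
|---|---|---|---|---|
| 60% | 43 | 4 | < 0.001 | 100 |
| 70% | 50 | 5 | 0.007 | 86 |
| 75% | 54 | 5 | 0.06 | 80 |
| 80% | 58 | 5 | 0.30 | 75 |
| 83.3% | 60 | 6 | 0.58 | 72 |
| 85% | 61 | 6 | 0.72 | 71 |
| 90% | 65 | 6 | 0.975 | 67 |

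The other outcomes have more room: walking ability can lose 72 − 50 = 22 patients (30.6%) and HRQoL 72 − 40 = 32 (44.4%).

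**3. What exchangeable GEE does with the mixture.** All inputs are assumed, and the scale is arbitrary. Patients measured at baseline go from 300 to 340, a change of 40. The others have no baseline value and score 200 at every follow-up. SD 80, within-patient correlation 0.6, everyone measured at each follow-up, no imputation, large sample. The estimate is the change from baseline at the first follow-up.

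| No baseline value | Difference of available means | GEE, 1 follow-up | GEE, 2 follow-ups | GEE, 4 follow-ups |
|---|---|---|---|---|
| 20% | 0.8 × 340 + 0.2 × 200 − 300 = 12 | about 27 | about 33 | about 36 |
| 30% | 0.7 × 340 + 0.3 × 200 − 300 = −2 | about 20 | about 32 | about 37 |

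A second setting, with a true change of 50 in everyone, three follow-ups, SD 100, correlation 0.6, and patients without a baseline value 100 to 150 units lower, gave about 47–48, 45–48 and 44–46 with 10%, 20% and 30% unmeasured at baseline.

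The planned correlation structure thus removes much of the distortion once there are several follow-ups, and less of it in a short-term report with one or two. It moves the estimate towards the change in those measured at baseline (40). It cannot recover the change in patients who have no baseline value if theirs differs.

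**4. HRQoL.** The three items of the global score cover function, problems with the prosthesis, and the overall situation as an amputee. The question put to non-users concerns the overall situation. I read it as the third item, so it should be available for users and non-users alike. The global score has no such common basis, yet it is the score described as continuous.

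**The case against.** The strongest case on the other side has four parts.

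- **The plan never says that GEE will run on observed values only.** It names imputation and a wheelchair stratum, and a journal article may leave analysis sets to a fuller document. This stands as far as the missing detail goes. What remains is a misfit between things that the article does fix: who is measured, the non-stratified main analysis, and mean change from baseline.
- **Exchangeable GEE with several follow-ups absorbs most of the composition effect.** This stands, and the calculation shows it. A reader might infer that the main estimates are badly biased. The documents do not support that: the size depends on shares they do not give, and figures from an independence structure or a plain difference of means describe an analysis that is not planned. Setting the estimate against a cohort mean with inability scored as zero would compare two different estimands.
- **The walking tests are not restricted.** This stands. A reader might infer that aided walkers also lack a 6MWT or TUG, but only kinematics exclude them, and the question on everyday walking distance can be put to anyone. That wheelchair-bound patients cannot do the tests is an inference, and the article does not say how they are scored.
- **Sixty may well be reached.** This also stands. A reader might infer that the kinematics model will fall short, but at 90% unaided walkers the chance of reaching 60 is 0.975. The supportable statement is conditional.

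**Conclusion.** The concern holds for kinematics and for the HRQoL global score. Patients without a baseline value are foreseen by the plan's own eligibility and strata, and neither imputation in general nor the wheelchair stratum gives them a usable comparison. The resulting estimate of change has no stated population. With several follow-ups it describes roughly those measurable at baseline while being presented as non-stratified; with one follow-up it also keeps a visible composition bias (about 20 to 27 against 40 in the assumed scenario).

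For sample size, the 60 is arithmetically right but is set against total accrual. It leaves a margin of 12 patients and needs at least 83% unaided walkers at baseline, a share that the plan does not state.

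The margin rests only on the documents' figures; the chances of reaching 60 and the size of the composition bias rest on assumed inputs. I also read the unaided-walker limit as covering both the video and the gyroscope methods, since both are described as ways of assessing the same kinematics. The point should be corrected, but it does not undermine the study as a whole.

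**What to change.** 1. **Kinematics.** Estimate change only in patients recorded unaided at baseline and at the follow-up concerned, and limit the conclusion to them. Report separately how many become measurable and how many cease to be at each visit.
2. **HRQoL.** Analyse the single overall question as the whole-cohort outcome, as an ordinal variable, and the global score only in patients who use a prosthesis at baseline.
3. **Imputation.** State that values which do not exist because the patient cannot walk unaided or does not use a prosthesis are not imputed; keep imputation for assessments that were missed.
4. **Sample size.** Restate the 60 as unaided walkers with a baseline recording, give the share observed so far, and allow one kinematics predictor per ten such patients.
5. **Optional.** If wheelchair-bound patients cannot perform the 6MWT or TUG, define an unable score, such as 0 m for the 6MWT and a worst category for the TUG. This would put a spike at 0 m in the distribution.

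The cost is revised analysis wording, one more categorical outcome in Aim 1 and a restated sample-size figure; no new data are needed. The downside is that the kinematic results apply to a defined subgroup and the sample-size figure becomes less favourable.
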